Furthermore, the investigational arm is unlikely to result in significantly more deaths, since palliation of symptomatic spine metastases is typically performed as part of routine care using RT. This treatment modality is widely utilized and well-established in this patient population and is highly unlikely to have more toxicity.

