### Schedule of assessments

The full schedule of assessments is described in Table 2. All included participants have objective confirmation of metastatic disease through either standard of care biopsy of a metastatic lesion or a radiology review documenting metastatic disease. Within 8 weeks (56 days) of trial entry, all participants will have had a (1) FDG-PET/CT scan or CT of the chest, abdomen, and pelvis; (2) MRI of the spine with and without contrast; (3) full medical history including comorbidities, current medications, and performance status; and (4) physical exam including vital signs (O_2_ saturation, blood pressure, heart rate, respiratory rate, and temperature), weight, and height. Following randomization, all participants in both study arms are scheduled for follow-up at 1 month (± 2 weeks), 3 months (± 4 weeks), 6 months (± 8 weeks), 12 months (± 12 weeks), and 24 months (± 16 weeks) and receive the following assessments: clinical evaluation, assessment of performance status, imaging studies, evaluation of AE (CTCAE v5.0) for individuals in arm 2, BPI Short Form, and EQ-5D (Table 3).

**Table 2 Tab2:** Schedule of assessments in the PROMISSED trial

Assessments*	Pre-enrollment	Baseline	Treatment	1-month F/U^1^	3-month F/U^1^	6-month F/U^1^	12-month F/U^1^	24-month F/U^1^
Informed consent	X							
Eligibility verification	X							
Physical exam	X^2^				X	X	X	X
Medical history	X^2^							
Performance status		X^3^			X	X	X	X
Skeletal related events (SREs)^4^								
Lesion identification worksheet^5^		X						
Numeric pain rating scale (NPRS)	X^6^		X^8^	X^9^	X	X	X	X
Neurological exam	X^6^				X	X	X	X
Imaging of the spine (MRI preferred, acceptable alternates include CT scan or bone scan)	X^7^				X	X	X	X
Documentation of patient’s pain medication^10^	X^6^							
BPI (QL)^11^		X			X	X	X	X
FACT-G (FA)^12^		X			X	X	X	X
EQ-5D (HP)^13^		X			X	X	X	X
Adverse event (AE) evaluation			X	X	X	X	X	X

*All the assessments will come from randomization. Therefore, both arms (arms 1 and 2) have the same timelines

^1^From randomization (times will be the same for intervention and without intervention) treatment. The window for the follow-up visits will be (1) 1 month ± 2 weeks; (2) 3 months ± 1 month; (3) 6 months ± 2 months; (4) 12 months ± 3 months; (5) 24 months ± 4 months

^2^Within 4 weeks before registration. Registration is considered when the eligibility is signed by the investigator

^3^Performance status can be collected before consent

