All participants in the upfront RT arm (arm 2) are evaluated for AEs according to CTCAE v5.0 and pain score using BPI short form once every five treatment days (typically at the time of their weekly on-treatment visit). Only participants in arm 2 (RT arm) are evaluated for radiation-related AE. In the event of an SRE, the following assessments will be attempted to be completed within 1 week. As it may not be feasible that the research team will be notified of all SREs within 1 week, or a participant may not be able to come to the institution, these assessments shall be considered optional but shall be endeavored for:Clinical examinationPerformance status assessmentImaging studiesAE evaluation (CTCAE v 5.0) for arm 2 participantsBPI Short FormEQ-5D-5L

For those participants that cannot come in for follow-up in-person visits or within 1 week of an SRE occurring, a telephonic assessment is considered sufficient, while clinical evaluation and imaging get postponed. Meanwhile, if the participant in this situation gets any of these assessments completed at another institution, efforts are made to obtain those records. If possible, the AE evaluation is also conducted through the telephonic assessment. If the participant in consideration is unable to complete Quality of Life Assessments, research staff are allowed to assist the patient. Furthermore, the BPI Short Form, the NPRS, and EQ-5D-5L in this case may be administered telephonically or directed to the patient through either postal mail, fax, or email by the physician, physician office assistant, or research staff. The mode of sending and receiving questionnaires is determined based on the participant’s preference. If participants cannot be reached through phone calls, the contact information on file will be used for a multipronged approach to get follow-up data.

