A Wilcoxon rank-sum test will be utilized to compare the number of hospitalizations secondary to SREs between the trial arms. For comparing the quality of life and pain level between the trial arms, we will assess at 3 months, 6 months, 12 months, and within 1 week of any SRE (optional). The individual and overall scores derived from the scales described previously will be summarized at these assessment points using means and standard deviations, or medians, and inter-quartile ranges. We will evaluate categorical variables from EQ-5D-5L between the trial arms using Fisher’s test at each time point as well, from which we will determine odds ratios with 95% confidence intervals. We will summarize other non-quantifiable answers (such as treatment received for pain control) in a descriptive fashion. For the score for pain interference on the BPI Short Form scale, we will consider it as the average of the seven interference questions as long as ≥ 4 questions are complete. The mean difference between the trial arms with regard to scores on these scales will be assessed for both statistical and clinical significance. This will be done using Wilcoxon rank-sum tests and established MCIDs. For scales lacking established MCIDs, the “half standard deviation” rule will be applied, wherein the differences of a half standard deviation in the scores between trial arms considered clinically meaningful. After the study is completed, we will plot data at each assessment point, including the number of trial participants in each arm, mean scale scores, and their trends over time. Based on this, we will consider utilizing more exhaustive regression analyses including generalized linear models. We will utilize log-rank tests to compare time-to-event endpoints such as PFS and OS. For toxicity, we will tabulate all AEs at 3, 6, 12, and 24 months post-randomizations in the early upfront RT arm.

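### The text restricts graded adverse-event evaluation and tabulation to arm 2, while the AE rows of Tables 2 and 3 carry no arm limit, so graded AEs have no control rate

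*Protocol article*

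**What the plan says.** All references are to the Protocol article.

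**Text, arm 2 only.**
- Schedule of assessments lists what participants in both arms receive at 1, 3, 6, 12 and 24 months, but qualifies one item: "evaluation of AE (CTCAE v5.0) for individuals in arm 2".
- The list of optional assessments after an SRE, in the same section, again gives AE evaluation for arm 2 only.
- The same section adds: "Only participants in arm 2 (RT arm) are evaluated for radiation-related AE".
- Planned statistical analysis states: "we will tabulate all AEs at 3, 6, 12, and 24 months post-randomizations in the early upfront RT arm".

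**Tables, no arm limit.**
- Table 2 has a single row, "Adverse event (AE) evaluation", marked at treatment and at 1, 3, 6, 12 and 24 months, with no footnote limiting it to one arm. The table's general note reads: "All the assessments will come from randomization. Therefore, both arms (arms 1 and 2) have the same timelines".
- Table 3 lists AE assessment at 1 month and at 3, 6, 12 and 24 months, also without an arm limit.

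**Definition and reporting.** Assessment of safety defines an AE irrespective of relatedness. It then confines reporting to events that a clinician judges definitely, probably or potentially related to protocol treatment. The randomization and blinding section makes clear that the trial is open label.

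**Expectation.** The last paragraph of Power calculation says of RT that it "is highly unlikely to have more toxicity".

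**The concern.** Arm 2 gives RT to patients who have no symptoms, or too few to need opioids, so its added toxicity matters to how the result is read. Patients in both arms also have progressing cancer and may receive systemic therapy. An AE table from arm 2 alone cannot separate RT effects from those background causes except through a clinician's causal judgement, made with knowledge of the treatment.

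Arm 1 is not free of RT either. Palliative RT is a component of the SRE endpoint, and the planning assumption is an SRE rate of nearly 60% within 1 year in that arm. Toxicity from deferred RT is part of what early RT should be weighed against, and the text makes no provision to record it.

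The gap is in collection, so a later analysis plan cannot close it. Staff who follow the tables would collect AEs in arm 1, and staff who follow the text would not.

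**Working it through.** **1. The places side by side**

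| Place | Who | When |
|---|---|---|
| Schedule text, follow-up visits | arm 2 | 1, 3, 6, 12, 24 months |
| Schedule text, after an SRE (optional) | arm 2 | within 1 week |
| Schedule text, on treatment | arm 2 | every five treatment days |
| Table 2, AE row | no arm limit | treatment, 1, 3, 6, 12, 24 months |
| Table 3 | no arm limit | 1, 3, 6, 12, 24 months |
| Planned statistical analysis | arm 2 | 3, 6, 12, 24 months |

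Three mismatches follow.
- *Arm:* the text says arm 2; the tables set no limit.
- *Time:* the toxicity table omits the 1-month assessment that both tables schedule, although acute RT reactions would be expected early.
- *Scope:* the analysis section promises all AEs, while Assessment of safety reports only those judged related.

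The sentence on radiation-related AEs is weaker evidence, because it does not itself exclude other AEs in arm 1. The restriction rests on the follow-up list, the post-SRE list and the tabulation sentence.

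**2. The plan's own sample size, which fixes the arm sizes**

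Inputs from Power calculation: SRE rates 0.60 and 0.30, one-sided alpha 0.05, power 80%, over-accrual 10%.

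n per arm = [1.645 × √(2 × 0.45 × 0.55) + 0.842 × √(0.6 × 0.4 + 0.3 × 0.7)]² / 0.30² ≈ 32.9, so 33 per arm and 66 in total. Power at 33 per arm is 80.1%. Then 66 / (1 − 0.10) = 73.3, so 74, or 37 per arm. The plan's figures reproduce. It gives no figure for toxicity.

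**3. Control patients who might receive RT**

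Assuming one lesion per patient and full follow-up, 0.60 × 37 ≈ 22 arm 1 patients would have an SRE by 12 months. The share of these that would be palliative RT is not stated. The rationale section cites a study in which bone RT was the most frequent procedure for SREs.

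**4. What a two-arm AE table would give**

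The document gives no AE rates, so the rates below are assumptions, taken as equal in both arms. Half-width of the 95% CI for the difference = 1.96 × √(2p(1 − p)/n).

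| Assumed rate p | n = 37 per arm | n = 33 per arm |
|---|---|---|
| 5% | ±9.9 points | ±10.5 points |
| 10% | ±13.7 | ±14.5 |
| 20% | ±18.2 | ±19.3 |
| 30% | ±20.9 | ±22.1 |

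For example, at 20%: 1.96 × √(2 × 0.2 × 0.8 / 37) = 0.182.

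At 37 per arm and two-sided alpha 0.05, power to detect 10% versus 20% is about 22%; 80% power needs about 10% versus 37%. With arm 2 alone, no between-arm difference can be estimated at any sample size.

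**The case against.** The strongest reply is that much of the relevant harm is already compared. Fracture is part of the primary endpoint, and spine imaging is scheduled for all participants. Pain is measured by BPI and NPRS, and quality of life by FACT-G and EQ-5D, with no arm limit in Table 2. Survival and SRE hospitalizations are compared by arm. This stands. A reader might infer that the trial has no comparative harm data at all, and the document does not support that. What lacks a comparator is CTCAE-graded AEs.

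A reader might also infer that the trial claims no added toxicity and cannot test its own claim. The sentence in Power calculation is an expectation about an established treatment. Toxicity is not among the listed endpoints, and no test of it is promised. The point is only that the expectation cannot be checked against AE data.

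The Table 2 note concerns the time origin. It implies AE collection in arm 1 but does not state it, and the AE row also covers on-treatment checks that the text describes for arm 2 only. The defect may therefore be an unannotated row. That stands as an explanation of the mismatch, but the two still need reconciling, and reading the tables down to the text leaves no control rate.

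It would also go too far to say that the monitoring committee sees no comparator. The article says that the committee reviews AE data under an institutional plan that is not shown, and it does not describe what those reports contain.

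Finally, two-arm collection at this size cannot establish equal toxicity. That is correct, and the gain is descriptive.

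**Conclusion.** The concern holds in a limited form. The text confines graded AE evaluation and tabulation to arm 2, and the AE rows of Tables 2 and 3 do not. The relatedness filter conflicts with the promise to tabulate all AEs, and the 1-month assessment is missing from the tabulation.

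Followed as written, the text yields no control rate for graded AEs and no record of toxicity after palliative RT in arm 1. Collecting in both arms would give differences with 95% CI half-widths of about 10 to 21 points at 37 per arm, and about 18 at an assumed 20% rate. These figures rest on assumed AE rates of 5% to 30% and on every randomized patient being assessed; losses would widen them. The primary SRE comparison and its sample size are unaffected.

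**What to change.** Reconcile Assessment of safety, the Schedule of assessments text, Tables 2 and 3 and Planned statistical analysis to one rule:

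- Collect CTCAE v5.0 AEs in both arms at the existing 1, 3, 6, 12 and 24 month visits, timed from randomization, and make the post-SRE AE evaluation apply to both arms.
- Include AEs that follow palliative RT given in arm 1.
- Tabulate AEs by arm regardless of relatedness, including the 1-month assessment, with risk differences and 95% CIs labelled as descriptive. Show relatedness separately.
- Because enrolment has begun, state the date from which arm 1 AEs are collected prospectively.

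The cost is extra AE form entry for about 37 arm 1 patients, at most 37 × 5 = 185 scheduled assessments before deaths and withdrawals. The visits already take place, and the protocol already allows AE evaluation by telephone. N stays at 74.

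If both-arm collection is not adopted, the minimum is to mark the AE rows of Tables 2 and 3 as arm 2 only, describe the AE data as uncontrolled, and remove the comparative toxicity statement from Power calculation. That removes the contradiction but leaves graded AEs without a comparator.

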### Ethical considerations, monitoring, and data confidentiality

The study protocol (2021-KOT-002) and informed consent documents were submitted to and approved by the WCG institutional review board (WCG IRB, Puyallup, WA, US, Study Number 1337188, IRB tracking number 20223735) on June 25, 2022. The study staff is responsible for ensuring that all institutional requirements necessary to enroll a participant in the study have been completed and protocol amendments are communicated to relevant stakeholders.

The institutional data safety and monitoring committee (DSMC) monitors this clinical trial according to the MCI data and safety monitoring plan. In its oversight capacity independent of study investigators, the DSMC bears responsibility for suspending or recommending this study. DSMC oversight of study conduct includes ongoing review of AE data. The DSMC reviews reports from all audits, site visits, or study reviews pertaining to this clinical trial and takes appropriate action. This study does not have criteria for stopping early. Therefore, no outcomes on data will be reviewed early.

Participant confidentiality and privacy is strictly held in trust by the participating investigators and their staff. The study protocol, documentation, data, and all other information generated are held in strict confidence. No information concerning the study or the data will be released to any unauthorized third party without prior written approval. All research activities are conducted in as private a setting as possible. The study participant’s contact information is securely stored in an electronic database for internal use during the study. Study participant research data, which is for purposes of statistical analysis and scientific reporting, will be transmitted to and stored at MCI. The study data entry and study management systems used by MCI research staff are secured and password protected. At the end of the study, patient data will be archived at MCI.

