### Assessment of safety

With regard to the assessment of the safety of the intervention, adverse events (AE) will be defined as any untoward medical occurrence associated with the use of an intervention in humans, whether or not considered intervention-related (21 CFR 312.32 (a)). All AEs will have their relationship to study intervention assessed by a clinician, who will examine and evaluate the participant based on temporal relationship and their clinical judgment. Only AEs that are definitely, probably, or potentially related to the protocol treatment will be reported. AEs will be classified according to the NIH Common Terminology Criteria for Adverse Events (CTCAE) version 5.0.

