### Discontinuation of study intervention

Early discontinuation is considered for a patient based on the patient’s and treating physician’s decision for standard of care therapies. Protocol treatment is discontinued when there is systemic or local progression of disease resulting in hospice enrollment.

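### The ban on early stopping criteria and early outcome review contradicts the listed grounds for ending the trial, and the article provides the DSMC no by-arm view of deaths, fractures or cord compressions

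*Protocol article*

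**What the plan says.** Under 'Ethical considerations, monitoring, and data confidentiality' the protocol article states: "This study does not have criteria for stopping early. Therefore, no outcomes on data will be reviewed early". The same paragraph gives the committee real functions. It "monitors this clinical trial according to the MCI data and safety monitoring plan", "DSMC oversight of study conduct includes ongoing review of AE data", and "the DSMC bears responsibility for suspending or recommending this study".

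'Study discontinuation and closure' then gives a non-exhaustive list of seven reasons for suspending or ending the trial. Among them are unacceptable risk to participants, efficacy strong enough to make continuation unethical, the primary endpoint having been met, and futility of the intervention.

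'Study endpoints' makes pathological fracture and spinal cord compression components of the primary endpoint, and death the event in overall survival.

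On adverse events, 'Assessment of safety' defines them broadly and has a clinician judge relatedness, but adds: "Only AEs that are definitely, probably, or potentially related to the protocol treatment will be reported". 'Schedule of assessments' says: "Only participants in arm 2 (RT arm) are evaluated for radiation-related AE". 'Planned statistical analysis' says: "we will tabulate all AEs at 3, 6, 12, and 24 months post-randomizations in the early upfront RT arm".

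**The concern.** Two things look wrong. First, a plan cannot both disclaim every early stopping criterion and list early stopping grounds, three of which depend on the outcome data it says nobody will look at. A DSMC member or auditor could not tell which section governs.

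Second, the sentence on early outcome review has no safety exception. In this trial the gravest spinal events are also the outcome: fracture and cord compression may come from the tumour, from radiotherapy, or from radiotherapy failing to prevent them. Judging relatedness case by case is difficult here, and the treating physician knows the allocation ('Randomization, blinding, and allocation concealment'). The concurrent randomized control arm is the natural check, and the article does not give the DSMC that comparison. The statement under 'Power calculation' that extra deaths and extra toxicity are not expected would then not be checked between arms while patients are being enrolled and treated.

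**Working it through.** No figure is in dispute, so the check is mainly a comparison of sections. The sample size does show which kind of design was planned.

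**Step 1: the design reproduces as a single-look test.** Inputs from 'Power calculation': event rates 0.60 and 0.30, one-sided 0.05, power above 80%, 1:1 allocation, 66 evaluable, 10% over-accrual, N = 74. The pooled-variance formula without continuity correction is

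n per arm = [z(0.95)·√(2·0.45·0.55) + z(0.80)·√(0.60·0.40 + 0.30·0.70)]² / 0.30²

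= [1.645·0.7036 + 0.842·0.6708]² / 0.09 ≈ 32.9, so 33 per arm and 66 in total.

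Power at 33 per arm is 80.06%. Over-accrual gives 66/0.90 = 73.3, rounded up to 74. The whole 0.05 is spent at one analysis. This agrees with having no interim analysis. It does not agree with stopping for efficacy or because the endpoint is met, since nothing is set aside for earlier looks.

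**Step 2: closure grounds against the ban.** What each of the seven listed grounds needs:
- Unacceptable risk: safety data. Compatible with adverse-event review, but hampered if fractures, cord compressions and deaths are withheld as outcomes.
- Proven efficacy: early outcome data by arm. Conflicts.
- Primary endpoint met: early outcome data. Conflicts.
- Futility: early outcome data. Conflicts.
- Protocol deviations, missing or unevaluable data, loss of funding: no outcome comparison. No conflict with the ban on outcome review.

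Three of seven grounds therefore cannot be applied while the ban stands. All seven sit awkwardly with the statement that no criteria exist.

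**Step 3: can the adverse-event stream supply the comparison instead?**
- Filter: only events judged at least potentially related are reported. A death or fracture attributed to disease drops out.
- Arm: evaluation for radiation-related events is confined to arm 2. The text of 'Schedule of assessments' also specifies the follow-up evaluation for arm 2.
- Output: the planned tabulation covers the radiotherapy arm only.
- Against this, Table 2 has an adverse-event row that names no arm, and its note gives both arms the same timelines. Some control-arm collection may therefore occur, but no section turns it into a comparison.

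Events judged related to radiotherapy can reach the DSMC from arm 2. Events judged unrelated, and the control-arm counts needed to interpret them, have no stated route.

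**The case against.** The strongest reply is that the disputed sentence means only that there is no interim outcome analysis. The same paragraph keeps adverse-event review running, under a committee independent of the investigators with responsibility for suspension and a separate institutional monitoring plan that is not shown. Discretionary review is a legitimate choice for 74 patients receiving established palliative regimens, and a condensed article need not print thresholds.

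Much of this stands, and it rules out several stronger readings that a reader might infer:
- *There is no protection against harm.* Not supported. Unacceptable risk is a listed ground, and the DSMC can suspend. Only a quantified threshold is absent from the article, and the monitoring plan may contain one.
- *The DSMC never sees fractures, cord compressions or deaths.* No section says so. The adverse-event definition is broad enough to include them, and those judged even potentially related could reach the committee.
- *All of the roughly 37 arm 2 patients (74/2) would be treated whatever the harm.* Not supported, because suspension is discretionary.
- *The rule for stopping an individual's treatment at hospice entry is the trial's only event-based safety rule.* That rule concerns individual treatment, not the trial, and is no evidence here.
- *A numeric pause boundary is needed.* The documents give no reference rate. Endpoint events accrue over 12 months, so early looks would miss many of them, and a single-arm rate cannot separate radiotherapy harm from disease.

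The reply does not remove the contradiction, because both sections are in the article and neither gives way to the other. Nor does the unshown plan settle the second part: if it provided early by-arm outcome review, it would contradict the article's sentence as written.

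**Conclusion.** The point holds in this form. The contradiction between the monitoring section and three of the seven closure grounds is plain on the text and needs no assumption. The gap in by-arm safety information rests on two readings: that the ban on early outcome review means what it says, without an implied safety exception, and that the restriction on reported adverse events applies to what the DSMC receives. On those readings, deaths, pathological fractures and cord compressions have no between-arm view during the two years of planned accrual and the follow-up after it. Under the narrower reading, that only a formal interim analysis is excluded, the article still does not say that the DSMC receives these events by arm. The size cannot be put as a number, because the documents give no harm rate. This is a correctable weakness in safety oversight and wording. It does not show that participants are unmonitored, and it does not affect the planned single-look test itself.

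**What to change.** 1. Reword the two sentences in the monitoring section along these lines: *No interim analysis for efficacy or futility is planned. At each of its adverse-event reviews the DSMC also receives, in a closed report by arm, all deaths, pathological fractures and spinal cord compressions, regardless of attributed relatedness.*

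2. Reconcile 'Study discontinuation and closure' with this. Keep the risk ground. Remove the efficacy, endpoint-met and futility grounds, or justify them and say what data and what error control would support them. Steps 1 and 2 belong together: the closed table shows part of the primary endpoint by arm, so it should not be usable for an unplanned efficacy stop.

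3. Leave the question of a numeric harm threshold to the sponsor and the DSMC. If the institutional monitoring plan already holds one, a cross-reference is enough.

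The cost is a short amendment and one extra closed table, from data already collected, for a committee that already exists. No more patients are needed. A review that can stop only for harm does not raise the one-sided type I error for superiority.
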